## Abstract

**Background:**

The school environment plays an essential role in promoting health education and physical activity for children and adolescence, and they are more likely to adapt it into their adulthood. School health education program has been endorsed and emphasized by the World Health Organization has not been implemented in true spirit in Pakistan yet. We aim to test feasibility of threefold health education program in children and its potential efficacy on physical activity and diet and cardiometabolic risk factors by including BP, BMI, and waist circumference.

**Methods:**

It is a parallel-group feasibility intervention trial. It is being conducted in two schools from lower to middle-income areas, at different locations but having the same school curriculum under the Aga Khan Education Service, Pakistan (AKESP). All children aged 9-11 years enrolled from the schools mentioned above were included. Children with any physical disability were excluded. One school received threefold intervention (focused on children, parents, and teachers) of school health education program in Pakistan (SHEPP) while the other school continued routine activity. Intervention of SHEPP is directed towards educating children, parents, and teachers about healthy behaviors. Children will receive interactive educational sessions and specially designed physical activity sessions. A 3-h health education session focusing on same healthy behaviors as for children will be conducted for both parents and teachers. Primary outcome is feasibility of SHEPP in terms of recruitment, retention, and treatment fidelity. Secondary outcomes are physical activity levels, dietary intake (of fruits, vegetable), and cardiometabolic risk factors (blood pressure, BMI, and waist circumference (WC)). The total number of children recruited were 982 (82.5 %); 505 from school A and 477 from school B and 496 (50.5) were boys.

**Conclusion:**

SHEPP is a unique health education program for children as it focuses on children while involving the parents and teachers in the behavior change process. If found feasible and demonstrating potential efficacy on physical activity, dietary behaviors, and cardiometabolic parameters, we will be able to replicate this on a larger scale in public sector schools also.

**Trial registration:**

NCT03303287

## Background

Cardiovascular diseases (CVD) top the list of the five leading causes of death globally [1]. CVD accounts for a third of the deaths in Pakistan [2]. In a lower-middle-income country like Pakistan, where an organized health infrastructure is still in infancy [3], the only cost-effective way to tackle this rising burden of CVD could be by providing health education to children and adolescents at a mass level about healthy lifestyle [4]. High childhood and adolescent BMI are associated with an increased risk of cardiovascular disease in adulthood [5]. Thirteen percent of children from Karachi, Pakistan, have been observed to be obese (higher BMI) and 21% had greater abdominal obesity.

Lack of adequate physical activity (PA) in children is a known risk factor of obesity. The recommended guideline for PA among children and youth (WHO, [6]) is that children and youth aged 5–17 should accumulate at least 60 min of moderate- to vigorous-intensity physical activity daily. But in a lower-middle-income country, like Pakistan, only 7% of the girls and 30% of the boys aged 13–14 years do the recommended physical activity of 1 h per day. About 66% of the children attending school reported that they did not participate in organized sport within school [7]. The reason for this inadequate physical activity include lack of spaces available for physical activity in school and out of school, cultural barriers for girls to do physical activity outside their house, less designated time for physical activity in school, and out of school by teachers and parents respectively (due to lack of awareness about benefits of physical activity) [8]. Approximately 85% of the students had a predominantly sedentary lifestyle, due to tuitions, television viewing, or internet surfing or indoor games like play stations in affluent schools of Karachi [9]. Additionally, a previous study from Pakistan has reported that unhealthy food, especially sugar-sweetened beverage consumption, and insufficient physical activity were associated with overweight and obesity [10]. Prevalence of smoking was reported to be 14% in adolescents aged 5-15 years from Pakistan [11, 12]. Additionally, the overall prevalence of smokeless tobacco and/or betel quid use is 42.6% in a study conducted on secondary school adolescents (*n* = 2140) [13].

Studies have been done to incorporate healthy behaviors in children like the good behavior game (GBG) to prevent the use of tobacco [14, 15]. The PAX version of the GBG (PAX GBG, developed by the Paxis Institute in the USA) was implemented in Estonia for the first time in 2014 by the Estonian National Institute for Health Development (NIHD) [16]. It is a classroom-based game where students are reinforced for their mutual success in withholding inappropriate behavior. As the preschool era in the life of a child plays an important role in developing healthy or unhealthy living patterns in adult life, designing of interventions to educate these adolescents about a healthy lifestyle is of prime importance in a lower-middle-income country like Pakistan.

Dietary or physical activity behavior produces a significant and clinically meaningful reduction in body mass index status of children and adolescents in preventing obesity [17, 18]. Additionally, school health interventions are effective in preventing smoking, and bullying [19]. While school health education program has been endorsed and emphasized by the WHO, it has not been implemented in true spirit in Pakistan. The health education that is provided is rather embedded within the course work and is not comprehended and does not add to behavioral change by children in the way it should. The main reason behind this lack of implementation of such programs is that public health education in Pakistan does not meet current national challenges which could regulate education, harmonize global standards to local context, or develop relevant career pathways [20]. Secondly, there is lack of rigorous evaluations of both educational content and programs in schools [21].

Theory of planned behavior is one behavior change theory that has demonstrated usefulness in studies of health-related behavior [22]. This suggests that educational strategies aimed at increasing children’s motivation remain an important strategy to promote physical activity. A review on the contextual influences on physical activity and eating habits of the community level reports that successful community-based health promotion strategies should consist of multilevel-multicomponent interventions on different levels of environments [23]. Such interventions in promoting a healthy lifestyle in children are targeting children, parents, and teachers simultaneously by introducing learning sessions and materials for a healthy lifestyle is useful [24, 25]. This threefold intervention including children, parents, and teachers is necessary as children learn behaviors from both school and home environment and if there is a disagreement between the two, the child might face conflicting behaviors that are hard to follow. We have previously shown the feasibility of a school-based physical activity program in a public sector girl’s school of urban Pakistan showing a favorable trend in BP and BMI at follow-up. However, the study did not include any health education intervention targeting children, teachers, or parents.

The aims of this study are the following:
To test feasibility of threefold health education program (on children, teachers, and parents) in school children.To test the potential efficacy of such a program on physical activity, diet, and cardiometabolic risk factors including BP, BMI, and waist circumference.

## Methods

### Study setting

It is a parallel-group feasibility intervention trial. The justification for a feasibility design is that this is the first study to incorporate health education, physical activity intervention in children involving parents, teachers, and children. Secondly, feasibility studies are relied on to produce a set of findings that help determine whether an intervention should be recommended for future efficacy testing or not [26]. This feasibility intervention design to test SHEPP is therefore justified. It is being conducted in two schools located in lower to middle-income class, at different locations but having the same school curriculum under the Aga Khan Education Service, Pakistan (AKESP). Each school has approximately 2000 students, both boys and girls. Each school comprises of 10 levels of classes with 3-4 sections each. These 10 levels of classes are similar to the Cambridge O Level (but the curriculum is locally adapted), where level of education increases with each increasing class from 1 to 10. Sections refer to groups of children sitting in separate rooms but at the same level of education. The study is expected to complete in 18 to 20 months. The study flow is shown in Fig. 1. All children aged 9-11 years enrolled from the abovementioned schools were included. The rationale for this age limit is that in this period of 9-11 years age, physical activity starts to decline mainly in girls [27]. Those suffering from any physical disability were excluded from this feasibility study. If found feasible, specific physical activity for disable children by using additional aids might be useful in future studies. These children however will attend the health education teaching sessions according to the principles of ethical justice.

**Fig. 1 Fig1:**
[figure not shown]
Study flow at baseline and follow-up at 12 months in the SHEPP

### Interventions

Intervention is the school health education program in Pakistan (SHEPP). SHEPP is directed towards children, parents, and teachers (Fig. 2). The basis of designing such intervention is to overcome cultural, socioeconomic barriers in performing physical activity [28]. The primary focus will be children. Intervention will be conducted within school premises over 10 months in one school while routine activities will be carried out in the control school. The 10 months cutoff has been chosen as benefits on cardiovascular risk factors are more pronounced at 10-month follow-up [29].

**Fig. 2 Fig2:**
[figure not shown]
School health education program in Pakistan (SHEPP)

### SHEPP-children

The SHEPP focusing on children comprises of physical activity sessions and healthy heart teaching.

#### SHEPP-physical activity sessions

These sessions in schools will comprise of total 140 min/week comprising of (a) 30 min twice a week delivered by teachers trained by physical trainers. It will be based on principle of warm-up, moderate to vigorous physical activity (games), and cool down [30] (30 × 2 = 60 min/week). This has been previously tested [30]. At least 12 different SHEPP-physical activity sessions have been designed for the participants. These were designed in coordination with the physical activity trainers of school. Every 30 min physical activity sessions comprise of 10-15 min structured exercise and 15-20 min games. (b) 10 min physical activity daily during assembly (10 × 5 = 50 min/week)*.* (c) 1 min between class physical activity (1 × 6 × 5 = 30 min/week) (Table 1: SHEPP physical activity sessions outline).

**Table 1 Tab1:** SHEPP-physical activity sessions

	Structured exercise	Games
Duration	10-15 min	15-20 min
*Level I* (*basic*)		
Session 1	Yoga	Ball with music or pass the ball
Session 2	Warm-up jogging	Race with ball
Session 3	Run and jump	Throwing stations
Session 4	Let us warm-up	Obstacle race
Session 5	Hopping race	Trees and squirrels
Session 6	Partner race	Couch potato tag
*Level II* (*advanced*)		
Session 1	Warm-up jogging Animal actions	Relay race
Session 2	Warm-up jogging Move and freeze	Lemon and spoon race
Session 3	Warm-up jogging	Hide and seek
Session 4	Warm-up jogging, aerobics	Running and catching (Pakram Pakrai)
Session 5	Warm-up jogging	Star war throwing game
Session 6	Warm-up jogging	Hopping race

#### SHEPP healthy heart teaching

This comprises 6 sessions of 30 min each. The sessions will be interactive using brief pictorial presentations, videos, and an activity to make it interesting for the children. In addition to healthy heart teaching additional stay clean and PAX, good behavior game will also be introduced to children. These additional sessions were identified as a “need” for the school children in preliminary discussions with teachers [31, 32]. The PAX GBG begins with creating a shared class vision displayed in the classroom for developing and maintaining a supportive classroom environment. The children will be introduced to good and bad (spleem) behaviors. Five teams will be made in each class with a team leader. A timer will be set during which children will be observed for good and spleem behaviors. The team which shows a spleem behavior will be given 1 mark. The team that has less marks at the end of the game will be the winner and will receive a prize at the end of the game. Examples of good behaviors are raising a hand when asking the teacher or doing work quietly while an example of spleem behavior is making noise or speaking without permission of the teacher [16]. Table 2 shows the outline of the SHEPP healthy heart teaching. The healthy heart teaching was based on resources from the American Heart Association (https://www.heart.org).

**Table 2 Tab2:** SHEPP healthy heart teaching

	Title	Description	Activity
Session 1	A happy heart; *what makes heart happy and what makes it sad*	What is the heart? Why is it important? What is good for the heart? What is bad for the heart?	Feeling of heart by hand Counting pulse of each other Checking pulse after spot jogging Ask them to pick pictures that are good for heart and bad for heart
Session 2	The smart diet	What is smart and healthy diet? My food plate	Pictures of food items given to children and they were asked to pick the healthy ones
Session 3	Keep moving	Why physical activity is good? Why using tablet/watching TV for long is bad? How to keep moving?	Ask them to jog, and how they feel (happy or sad) Speak up on watching TV or watching tablet
Session 4	Smoking cigarette or chewing “gutka” is bad for health	Why smoking cigarette is bad? What is second-hand smoking? Is it harmful?	Ask all students to write 2 harmful effects of smoking
Session 5	Stay clean, stay healthy	Why do hand washing? Why brushing teeth is important?	Perform and demonstrate in front of class correct way of washing hands and brushing teeth
Session 6	Pax good behavior game	Make children learn good class behaviors Make note of not so good class behaviors Not point out any child on bad behavior Only point teams Appreciate with Pax action prize	Playing Pax behavior game

### SHEPP-teachers

The SHEPP for teachers is based on the same core topics as shown in Table 2; however, some of the topics were changed to make it more relevant for the teachers (as they were adults). Thirty teachers involved in teaching the respective classes as recommended by the school principal will be invited. The 3-h interactive workshop will be conducted on a weekend when teachers had come for other administrative work in school. The workshop will be delivered by trained research staff under the close supervision of the primary investigator. A teaching manual for the teachers will also be developed with a table of specifications for different sections of the workshop. The outline of the workshop is shown in Table 3. The teaching methods included (1) presentations by facilitators, (2) interactive discussion between facilitators and teachers, (3) healthy physical activity during workshop, and (4) discussion on personal stories of teachers. There will be no formal competency assessment of the teachers on their understanding of the SHEPP due to resource and time constraints, but ideally should be incorporated in future larger studies to encourage participation in the workshop a free health checkup for the teachers including blood pressure measurement, glucose monitoring, height and weight measurements (BMI calculation) will also be offered. These services will be provided by other allied health workers.

**Table 3 Tab3:** SHEPP for teachers and parents

Topics	Subtopics	Time duration
1. The heart attack!	What does the heart do and how? Understand how blockage occurs in coronary arteries and why you should care. What is heart attack or disease? Risk factors for CAD	30 min
2.What is healthy diet	What is meant by a healthy diet? My food plates Daily calorie requirement Hints for healthy eating	30 min
3.Keep moving and stay active	Why moving and staying active is important? Sitting and using mobile phones/computer/watching TV is bad What are the recommendations and how to move?	30 min
4. Why smoking, “gutka, shisha and chaalia” is bad	Why smoking is harmful? Shisha, gutka, and chalia Ways to quit smoking	30 min
5. Wash your hands always!	Proper hand hygiene Dental hygiene	30 min
6. Stay calm, stay away from anger and stress	Anger and stress How to be less stressed and less angry	30 min

### SHEPP-parents

The SHEPP for parents is based on the same outline as for teachers (Table 3). Parents will be invited twice on a weekend to attend a 3-h healthy heart teaching. This will be done by the team of trained staff and a physician. To encourage in the workshop a free health checkup for the parents including blood pressure measurement, glucose monitoring, height and weight measurements (BMI calculation) will also be offered

### SHEPP-routine activity in control group

The school in the control group will carry on routine physical activity in school which is a 30-min physical activity as per schedule in school. For ethical reasons (1) a workshop for teachers will be held as for SHEPP teachers in the intervention arm towards the end of the study, (2) health education posters will be placed in school classes towards the end of the study, (3) a large class format combined health tips (on physical activity and diet) will be held for all children after completion of study.

## Adherence to SHEPP

A logbook will be maintained to track SHEPP-physical activity and healthy heart sessions for children. The adherence will be measured in terms of percentage of sessions attended by the children. To improve adherence physical activity leaders will be selected from each class and will be given a badge of physical activity leaders. Additionally, after completion of the initial 12 sessions of physical activity, children will be asked “If they had any other games they wanted to play” and these will be incorporated into the SHEPP physical activity sessions. To improve adherence to intervention of SHEPP for teachers and parents, free health checkups will be conducted along with healthy heart sessions.

## Outcome measures

### Measures of feasibility

Feasibility of SHEPP in terms of recruitment, retention, and treatment fidelity will be assessed. *Recruitment* is defined as the percentage of participants enrolled out of the total participants who were invited at baseline. *Retention* is defined as the percentage of participants who will be available for follow-up at 10 months out of those recruited at baseline. *Treatment fidelity* will be defined as the proportion of planned physical activity sessions held [33]. The trial will be considered as feasible if recruitment, retention, and treatment fidelity are > 70% recruitment [34].

Measure of potential effect

Physical activity levels (in school, out of school, moderate to vigorous physical activity, and sedentary time) assessed by change in time (minutes) spent in physical activity. Dietary patterns in terms of percentage increase in fruits and vegetable serving/day, and percentage decrease in sweetened beverages and snacks/day, cardiometabolic risk factors by change in BP, BMI, and waist circumference (WC).

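### The aim is feasibility of a threefold programme, but the feasibility rule counts only children recruited, children retained and physical activity sessions held

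*Protocol article*

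**What the plan says.** The first aim, at the end of the Background, is "To test feasibility of threefold health education program (on children, teachers, and parents) in school children". The abstract's Methods paragraph makes this the main endpoint: "Primary outcome is feasibility of SHEPP in terms of recruitment, retention, and treatment fidelity".

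Measures of feasibility then defines the three terms:

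- Recruitment is the share of those invited who enrol.
- Retention is the share of those enrolled who can be followed up ten months later.
- For fidelity, the article's wording is that it "will be defined as the proportion of planned physical activity sessions held".

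The trial is to be called feasible if all three exceed 70%.

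The programme itself is wider. Besides physical activity, children receive six 30-minute healthy heart sessions (SHEPP healthy heart teaching). For the teacher workshop, "Thirty teachers involved in teaching the respective classes as recommended by the school principal will be invited". For parents, "Parents will be invited twice on a weekend to attend a 3-h healthy heart teaching".

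On records, the section Adherence to SHEPP states "A logbook will be maintained to track SHEPP-physical activity and healthy heart sessions for children", and it measures adherence as the percentage of sessions that children attend. Methods: monitoring repeats that healthy heart and physical activity sessions will be logged. Neither section links these records to the feasibility rule.

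**The concern.** A feasibility criterion should be able to fail when the thing being tested fails. Here the thing being tested has three target groups and includes health teaching, while the only delivery measure in the rule concerns physical activity.

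The parts left out are the ones the article uses to justify the study. The Background says the group's earlier physical activity study had no health education for children, teachers or parents. Study setting justifies the feasibility design by the combination of health education and physical activity involving all three groups. The Discussion places the study's importance in the inclusion of parents and teachers.

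Parent turnout is also an evident uncertainty, since the teaching takes three hours at a weekend and free health checks are offered to encourage attendance. At stake is what the primary conclusion means: a favourable verdict could be read as evidence that the threefold programme can be delivered when the rule never looked at most of it.

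**Working it through.** The article gives no calculated figure to reproduce for this point. The check applies the stated rule to the programme's components and then to one scenario.

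**1. Which components can move the verdict?**

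| Component | Where described | Enters the >70% rule? |
|---|---|---|
| Children enrolled out of invited | Measures of feasibility; Recruitment | Yes, as recruitment |
| Children available at 10 months | Measures of feasibility | Yes, as retention |
| Physical activity sessions held | SHEPP-physical activity sessions | Yes, as fidelity |
| Six healthy heart sessions | SHEPP healthy heart teaching | No |
| Teacher workshop, 30 invited | SHEPP-teachers | No |
| Parent teaching, two invitations | SHEPP-parents | No |
| Children's attendance at sessions | Adherence to SHEPP | No; measured, without a threshold |

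That recruitment refers to children follows from the Recruitment section, which reports 982 children recruited after forms went to 1191 eligible families.

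**2. Scenario.**

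- Recruitment: 982/1191 = 0.8245, the stated 82.5%. This is already above 70%.
- Retention: suppose it exceeds 70%.
- Fidelity: suppose more than 70% of planned physical activity sessions are held.
- Healthy heart sessions given: 0 of 6. Teachers attending: 0 of 30. Parents attending: none.

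All three criteria are met and the rule returns feasible.

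**3. How much teaching is outside the rule?** If each of the 12 intervention classes (Sample size) receives all six sessions, 6 × 12 = 72 class-sessions carry no weight. Neither do the teacher workshop or the parent sessions.

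**4. Would one pooled percentage of all sessions cure this?** No. The article gives a 10-month intervention but no count of school weeks, so assume 30 to 43. Counting only the two 30-minute physical activity sessions per week, a class has 2 × 30 = 60 to 2 × 43 = 86 of them. The teaching occasions number about 6 + 2 + 1 = 9 (child, parent, teacher). With all physical activity held and no teaching given:

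- 60/(60 + 9) = 87%
- 86/(86 + 9) = 91%

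Both are well above 70%. Counting assembly and between-class activity as well would raise them further. The components must stay separate.

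**The case against.** The strongest replies, and what stands of each:

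- **Scale-up needs more than feasibility.** This stands. A reader might infer that a programme no parent attended would be expanded on this rule alone. The article does not say that: the abstract's Conclusion and the final Conclusion also require potential effects on physical activity and dietary behaviours, and the abstract adds cardiometabolic parameters. Limitations treats behaviour change as an indirect check on the teaching. These are still not measures of delivery.
- **Delivery of teaching is recorded.** This largely stands. The log under Methods: monitoring is not limited to children, and the article also uses the term healthy heart sessions for teachers and parents, so it may show whether their sessions were held. A record outside the rule does not change the verdict, however.
- **Attendance is handled as adherence.** This stands as a design choice. Separating delivery from receipt is legitimate. Child attendance is measured, and Adverse events defines non-adherence and drop-out. Neither enters the rule, and parent and teacher attendance has no stated measure.
- **Physical activity delivery was a real question.** This stands. A reader might infer that the rule merely repeats what was already shown. The earlier study was in a public-sector girls' school, whereas these schools are mixed, and Limitations reports that the schools would not allow four sessions a week. Including physical activity is right; including nothing else is the problem.
- **Assembly and between-class activity.** A reader might infer that these minutes are also uncounted. SHEPP-physical activity sessions lists them within the 140 minutes a week of sessions, so this is at most an ambiguity to settle.
- **The article condenses a fuller protocol.** A fuller document may well define parent or teacher attendance. The point does not rest on that absence: the article states a complete rule, and that rule does not match its own aim.

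**Conclusion.** The stated rule does not answer the stated primary question. It can return feasible with no health teaching given and no teacher or parent attending, and one of its three conditions is already met at 82.5%. This follows from the definitions and needs no numerical assumption. Only two side figures rest on assumptions: the 72 class-sessions (six sessions in each of 12 classes) and the 87% to 91% range (30 to 43 school weeks).

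The documents do not support saying that teaching would go unrecorded, that child attendance is ignored, or that a pass would by itself lead to expansion. The data to be collected remain usable. What fails is the inference from a pass to a deliverable threefold programme, so the definition should be changed before follow-up.

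**What to change.** In Measures of feasibility, replace the single fidelity definition by one for each component, reported separately and not pooled:

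1. Physical activity sessions held out of planned, stating that the assembly and between-class parts count.
2. Healthy heart class-sessions held out of planned (72 if all 12 classes receive six).
3. Teachers attending out of the 30 invited.
4. Intervention-school children with a parent attending, out of those recruited in that school.

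Report child attendance from the existing adherence measure beside these.

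Before follow-up, fix a criterion for each component. The plan's own >70% could serve for sessions held; the investigators should set the one for parent attendance. Limit the feasibility conclusion to the components that were assessed and met their criterion. Requiring every component to pass before any favourable conclusion is drawn is a stricter option, not a necessity; naming the components that were feasible is enough to cure the mismatch.

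The cost is small: sign-in sheets at the teacher and parent sessions and a change of wording, since the children's sessions are already logged. Delivery is described in the future tense, so the article treats it as still to come. If some attendance data cannot be obtained, the conclusion should leave that component out. The real price is that a claim of threefold feasibility becomes harder to reach.
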